### Sample size calculation

The sample size calculation is based on a previous psychological intervention research aimed at reducing breast cancer patients' FCR, with an effect size of *d* = 0.49 (46). The power analysis program G^*^Power was used to calculate the sample size. At least total 134 participants (67 participants in each group) need to be included to detect an effect of *d* = 0.49 with a power of 0.8 and two-side *alpha* level of 0.05. Considering the dropout of participants, we added 20% of the sample size. Therefore, this study needs a total of 160 participants, with 80 participants in each group.

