### Randomization

A table of randomized number will be generated by using the SAS. According to the table of randomized number, participants will be randomized to the intervention or control group with an allocation ratio of 1:1, after stratified by age, cancer stage, and breast cancer subtype. Participants will not know which group they will be allocated in.

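### Enrolling 160 falls short of the plan's own minimum of 134 after a 20% loss, because the dropout allowance was computed as 134 × 1.2 and rounded down

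*Protocol article*

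**What the plan says.** Under Sample size calculation, the protocol article takes a standardised effect of d = 0.49 from an earlier trial and sets the operating characteristics "with a power of 0.8 and two-side *alpha* level of 0.05". From these it concludes: "At least total 134 participants (67 participants in each group) need to be included". The dropout step is one sentence: "Considering the dropout of participants, we added 20% of the sample size". The result is that "this study needs a total of 160 participants, with 80 participants in each group". The Randomization section confirms equal allocation, "with an allocation ratio of 1:1".

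No expected dropout rate is given as such, in this section or elsewhere in the article. Power of 0.8 is attached to the 134, not to the 160 after losses.

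**The concern.** An allowance for dropout exists so that, once the anticipated patients are lost, the number required for the stated power remains. Adding a percentage to n does not do this for a loss of the same percentage, because the loss is taken from the larger, enrolled number. The inflated figure is also a minimum, so a fraction should be rounded up. Here the figure was obtained by addition and then rounded down. If 160 does not preserve 134, readers of the protocol, and later of the trial report, will credit the trial with more tolerance for dropout than it has.

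**Working it through.** **Inputs** (all from Sample size calculation, except the allocation, from Randomization): d = 0.49; two-sided alpha 0.05; power 0.80; allocation 1:1; minimum 134 (67 per group); 20% added in view of dropout; final 160 (80 per group).

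**1. Reproduce the base figure.** For a two-sample t-test with n per group, power comes from the noncentral t distribution with 2n − 2 degrees of freedom and noncentrality d × √(n/2).
- n = 66: 0.49 × √33 = 2.815, power 0.798
- n = 67: 0.49 × √33.5 = 2.836, power 0.804

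So 67 per group is the smallest n that reaches 0.80, and the plan's 134 is right. (A normal approximation gives 66 per group.)

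**2. Reproduce the 160.**
- By addition: 134 × 1.2 = 160.8 (67 × 1.2 = 80.4 per group). Rounded down, this is the plan's 160 (80 per group). Rounded up, it is 161, or 162 with equal groups (81 each).
- By division by the retained share: 134 / (1 − 0.20) = 167.5, so 168 (84 per group). This does not give 160.

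Only the addition, rounded down, reproduces the plan. The increase actually made is 26 patients, or 26/134 = 19.4% of 134.

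**3. If 20% is the dropout rate.** 160 × 0.80 = 128 evaluable, 64 per group, and 134 − 128 = 6 short. At n = 64 the noncentrality is 0.49 × √32 = 2.772 and power is 0.785 (0.792 by normal approximation). The effect detectable with 80% power at 64 per group is d = 0.499.

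**4. If 20% is only an addition to n.** Adding 20% offsets a loss of 1 − 1/1.2 = 16.7%. Then 160/1.2 = 133.3 remain, below 134. The shortfall comes wholly from rounding 160.8 down. Its effect on power is negligible: even 66 per group gives 0.798.

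**5. What 160 does tolerate.** (160 − 134)/160 = 26/160 = 16.25%, i.e. 13 losses in each group of 80.

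**The case against.** The strongest reply is that the article never says it expects 20% dropout. It says that 20% was added, and read literally that is almost what was done: the discrepancy is 0.8 of a patient, or two patients with equal groups. The six-patient shortfall and the figure of 168 both rest on an inferred rate. This stands, and the point must be worded conditionally. It does not remove the point, because the sentence ties the 20% to dropout, gives no other rate, and on the literal reading still leaves fewer than 134.

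A second reply is that 0.785 is not the power of the planned analysis. It belongs to an unadjusted t-test on completers. The Statistical analyses section specifies linear mixed models over four post-baseline time points with the baseline score as a covariate. Such a model can use partial follow-up, so 20% dropout need not mean only 128 patients analysed. Baseline adjustment also reduces residual variance by a factor of roughly 1 − r², where r is the correlation of baseline with follow-up. On that approximation, 128 adjusted patients match 134 unadjusted ones once r = √(1 − 128/134) ≈ 0.21. The article gives no r, so this is an assumption: r = 0.2 gives 128/0.96 = 133.3, almost closing the gap, and r = 0.3 gives 128/0.91 = 140.7, more than closing it. This also stands, so any restated power should name its basis. It does not correct the arithmetic, since the article justifies 160 from d alone and claims no gain from adjustment.

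A third reply is that a move from d = 0.49 to 0.50 is trivial beside the uncertainty of an effect taken from one earlier trial, which the Introduction itself describes as small. That is fair, and it limits the severity.

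**Conclusion.** The allowance as computed does not preserve the plan's stated minimum on either reading of the 20%. If 20% is the dropout rate, the shortfall is six patients and power is 0.785 against 0.804 at 67 per group. If it is only an addition to n, the shortfall is under one patient. The power figures assume d = 0.49, losses spread equally over the groups, and the unadjusted two-sample t-test behind the plan's own 134. This is a minor arithmetic error; the design is not undermined.

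A reader might infer that the plan claims 80% power after 20% dropout and that the claim is false. The article does not support that: it states no dropout rate and claims power 0.8 only for 134, which is correct. A reader might also infer that the trial's real power is 78.5%, but the planned analysis is a different one whose power the article gives no means to compute. Nor can the exclusion of patients with recurrence or the delivery of therapy in groups be added to the size of this error. The article gives no recurrence rate or intraclass correlation, and these are separate matters.

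**What to change.** Keep 160 and replace the dropout sentence. Suggested content: enrolling 160 patients (80 per group) preserves the required 134 evaluable patients for dropout up to about 16%; at 20% dropout (128 evaluable) power is about 78.5% for d = 0.49 on the unadjusted two-sample t-test used for the calculation, and the baseline-adjusted mixed model may recover some of this. The article should also say whether 20% is the dropout rate expected.

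The cost is one restated sentence and a slightly less favourable stated tolerance. Enrolment, design and analysis do not change. If the sponsor wants 20% dropout covered in full on the same basis, the figure is 134/0.8 = 167.5, so 168 (84 per group), eight more than planned.

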### Statistical analyses

The aim of the primary analysis is comparing the Fear-focused Self-compassion Therapy group with usual care control group on the score of FCRI severity subscale. In the primary analysis, post-treatment scores will be compared between two groups at four measurement time points (T1, T2, T3, and T4). Analysis will be performed by using linear mixed models, including baseline scores, sociodemographic and medical variables as covariates.

The aim of secondary analysis is to test the mediating role of improved dysfunctional cognitive evaluation and improved functioning of autonomic nervous system between Fear-focused Self-compassion Therapy and improved FCR. Analysis will be performed by using multilevel structural equation model, including baseline scores, sociodemographic and medical variables as potential covariates.

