In the context of cancer, the beneficial role of self-compassion on psychological outcomes (including symptoms of depression, anxiety, and fatigue) has been confirmed in Chinese cancer patients (43, 44). As for FCR, intervention studies have started to examine the feasibility of self-compassion therapy in the application of coping with FCR (45, 46). Using randomized controlled trails, two studies focused on middle aged and elderly breast cancer patients, and confirmed that an 8-week self-compassion intervention was feasible and acceptable for these patients to decrease levels of FCR by enhancing one's self-compassion (45, 46). Yet, given the inclusion of middle aged and elderly breast cancer patients from the Western countries and the use of small sample size, it remains unclear to what extent their conclusions can be generalized into young breast cancer patients in China. Moreover, the two previous studies only examined the short-term (i.e., no longer than 6 months) efficacy of self-compassion related therapy on FCR, and it remains unknown about the long-term (i.e., longer than 6 months, such as 12 months after intervention) effectiveness and why self-compassion related therapy would be effective in reducing severe FCR.

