### Aims of this study

In the current study, the Fear-focused Self-compassion Therapy, aiming to help Chinese young breast cancer patients to address FCR, has been developed. The primary aim of the current randomized controlled trial is to evaluate the effectiveness (i.e., both short-term and long-term effectiveness) and cost-effectiveness of Fear-focused Self-compassion Therapy in reducing severe FCR in young women with breast cancer, compared to usual care. Due to a lack of research comparing the cost-effectiveness between compassion-based therapy and usual care, it is hard to hypothesize which condition would be more cost-effective. This study expects that Fear-focused Self-compassion Therapy would be more cost-effective than usual care by reducing patients' FCR more effectively. Several specific hypotheses were outlined:

FCR severity would reduce to a larger extent in the Fear-focused Self-compassion Therapy condition (intervention group) compared to the treatment as usual condition (control group) from baseline and follow-up (3 months after treatment). The improvements in FCR can maintain at least 6 months after treatment.Symptoms of depression and anxiety would reduce to a larger extent in the Fear-focused Self-compassion Therapy condition compared to the treatment as usual condition from baseline and follow-up (3 months after treatment). These effects can maintain at least 6 months after treatment.Fear-focused Self-compassion Therapy would be cost-effective compared to treatment as usual.

The secondary aim of this study is to examine the underlying mechanisms of Fear-focused Self-compassion Therapy in reducing severe FCR. Specifically, the current research assumed that patients' improved dysfunctional cognitive evaluations and improved functioning of autonomic nervous system would play mediating roles between Fear-focused Self-compassion Therapy and improved FCR. Specific hypotheses are:

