#### Primary outcomes

Fear of cancer recurrence will be assessed using 42-item Fear of Cancer Recurrence Inventory (FCRI). This questionnaire consists of seven subscales, with a total score representing one's levels of FCR. A score of 13 or higher on 9-item severe subscale (ranges from 0 to 36) indicates a clinical FCR. The FCRI has been shown to have a good validity (convergent validity *r* = 0.68–0.77) and reliability (Cronbach's *alpha* = 0.95) (49).

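### The primary analysis gives four visits equal standing, while hypothesis 1 is set at 3 months and the sample size covers one two-sided test

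*Protocol article*

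**What the plan says.** All references are to the protocol article.

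- **Statistical analyses.** The arms are compared "on the score of FCRI severity subscale", and "post-treatment scores will be compared between two groups at four measurement time points (T1, T2, T3, and T4". The method is given as: "Analysis will be performed by using linear mixed models, including baseline scores, sociodemographic and medical variables as covariates". No visit is ranked above another.
- **Aims of this study.** Hypothesis 1 expects a larger reduction in FCR severity in the therapy arm "from baseline and follow-up (3 months after treatment", and adds: "The improvements in FCR can maintain at least 6 months after treatment". On the visit schedule this is T2, followed by T3. The primary aim in the same section covers both short-term and long-term effect.
- **Introduction.** Long-term is explained as "long-term (i.e., longer than 6 months, such as 12 months after intervention", which corresponds to T4.
- **Sample size calculation.** An effect of d = 0.49, power 0.8 and two-sided alpha 0.05 give 67 per group and 134 in total, raised to 160 for dropout. Neither a visit nor a scale is attached to d.
- **Primary outcomes and Table 2.** The table lists the FCRI without a subscale. The text says of the 42-item instrument: "This questionnaire consists of seven subscales, with a total score representing" the level of FCR. It mentions the severity subscale only for the clinical cut-off of 13. The Abstract names FCR severity as the primary outcome.

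**The concern.** A confirmatory trial needs its hypothesis, its primary comparison and its sample size to refer to the same test. Here the hypothesis points to T2 and then T3, the analysis gives T1 to T4 equal weight, and the sample size pays for one comparison at the full 0.05. A reader of the final report could not tell from this article which result decides whether the trial succeeded.

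At stake is what may be claimed. If the visits differ, for example with an effect at T1 that has faded by T3, the plan as worded allows this to be presented as a positive or a negative primary result, and the choice could be made after the data are seen.

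**Working it through.** **Inputs.** From Sample size calculation: d = 0.49, two-sided alpha 0.05, power 0.80, 67 per group. From Statistical analyses: four visits. The documents give no correlation between the visit-specific comparisons, so I assume one common value and vary it from 0.3 to 0.9. I also assume d = 0.49 and 67 evaluable per group at every visit.

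**1. The plan's own figure.** The normal approximation gives n = 2 × (1.960 + 0.842)² / 0.49² = 2 × 7.85 / 0.2401 = 65.4, so 66 per group. The noncentral t calculation gives 66.35, so 67 per group and 134 in total, with power 0.804. The stated figure is reproduced. A one-sided test would need only 53 per group, so the figure is one two-sided comparison with undivided alpha.

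**2. If any one visit suffices.** With independent tests the chance of at least one false positive is 1 − 0.95⁴ = 0.185. With correlated tests it is the probability that the largest of four |z| values exceeds 1.96 under no effect (simulation, 2 million draws).

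**3. If all four visits are required.** Each z statistic has mean 0.49 × √(67/2) = 2.84. Joint power is the probability that all four exceed 1.96. The normal statistic is slightly generous: single-visit power is about 0.81, against 0.804 by the t test.

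| Assumed correlation | False-positive rate, any visit | Power, all four visits |
|---|---|---|
| 0.3 | 17.4% | 0.51 |
| 0.5 | 15.6% | 0.57 |
| 0.7 | 13.1% | 0.63 |
| 0.8 | 11.4% | 0.67 |
| 0.9 | 9.4% | 0.71 |

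Under the all-four rule there is no inflation of the false-positive rate. Under the any-visit rule power is not the difficulty. Neither rule gives both 5% error and 80% power.

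**4. Possible repairs.**

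- *Bonferroni over four visits:* alpha 0.05/4 = 0.0125 requires 94.46, so 95 per group and 190 evaluable. With 67 per group, power at each visit falls to 0.620.
- *One primary visit at 0.05:* 67 per group and power 0.804, as planned.
- *T2, then T3, then T4 in fixed order, each at 0.05:* power for T2 stays at 0.804 and no alpha is divided. The chance of passing all three is about 0.59 to 0.73 for correlation 0.3 to 0.9, with the same d at each visit.

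**The case against.** Four arguments can be made for the plan as it stands.

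1. *Order of testing and multiplicity rules are commonly left to the SAP or full protocol, and neither is shown.* This is correct, and their absence is not the point here. The point is that the article's own statements differ. An SAP that names one visit would have to depart from either the Aims or the Statistical analyses section.
2. *The primary aim covers short and long term, so comparing at every visit serves it.* This stands as a reason to measure and report at all four visits. It does not say which visit decides.
3. *A linear mixed model allows a single group effect or a joint group-by-time test.* It does, and such a contrast would also be a legitimate primary test. The article, however, describes comparisons at four visits and selects no overall contrast.
4. *No passage says that success at one visit makes the trial positive.* This stands in full, so the false-positive rates in the table are conditional on that rule.

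A reader might also infer that the long-term claim has no test at all. The documents do not support this: T4 is one of the four visits in the primary analysis. Hypothesis 1 does not name T4, but its lower bound of 6 months does not exclude it. What is missing is a rank for T4.

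**Conclusion.** The point holds as a mismatch between stated sections: four visits of equal standing in the analysis, a hypothesis set at 3 months with maintenance to at least 6 months, and a sample size for one test. Its size is about 9% to 17% false-positive risk if any visit suffices, or about 0.51 to 0.71 power if all are required. These ranges rest on an assumed common correlation of 0.9 to 0.3, and the power range also on d = 0.49 with 67 per group at every visit.

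Three stronger readings are tempting but not supported:

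- *The trial was sized for 3 months.* The sample size section names no visit. Only the hypothesis does.
- *The error rate exceeds 5% in any case.* It does so only under an any-visit rule, which the article neither states nor excludes.
- *There are two primary scales, so the number of primary tests doubles.* The Statistical analyses section fixes the severity subscale, the Abstract agrees, and no section plans a between-arm test of the FCRI total. The Primary outcomes section describes how the instrument is scored. It needs aligning, but it does not add tests.

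**What to change.** Before outcome data are seen:

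- In Statistical analyses, name one primary contrast. The natural choice is the between-arm difference in FCRI severity at T2, the hypothesised time, from the mixed model at two-sided 0.05.
- Test T3 and then T4 in fixed order at 0.05, each only if the preceding test is significant, to support the maintenance and long-term claims. Make T1 secondary.
- State in Sample size calculation that the 134 evaluable participants refer to this contrast.
- Minor: in Primary outcomes and Table 2, name the severity subscale as the primary outcome, in line with the Abstract and Statistical analyses.

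The cost is wording only. The 134 evaluable participants and power 0.80 are kept, whereas Bonferroni over four visits would need 190 evaluable. The downside is that an effect at T1 alone could not be claimed as the primary result, and a failure at T2 would close the confirmatory tests at T3 and T4. An averaged or joint contrast over the visits would also resolve the conflict if the investigators prefer it, but hypothesis 1 would then have to be reworded to match.

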## Discussion

This RCT will be conducted with two aims. The primary aim is to evaluate the short-term and long-term effectiveness and cost-effectiveness of Fear-focused Self-compassion Therapy for reducing severe FCR in young women with breast cancer. The secondary aim is to examine whether improved dysfunctional cognitive evaluation and improved functioning of the autonomic nervous system would play a mediating role between Fear-focused Self-compassion Therapy and improved FCR.

### Strengths and weaknesses

This RCT of Fear-focused Self-compassion Therapy has several strengths. First, given that most of previous research focused on middle aged and elderly cancer patients, this study could fill the knowledge of the application of Fear-focused Self-compassion Therapy in young breast cancer patient population. Second, this study examines the long-term effectiveness of Fear-focused Self-compassion Therapy for patients' FCR, to verify whether this intervention is valid for controlling FCR in a long period of time. Third, by verifying the mediating role of dysfunctional cognitive evaluation and autonomic nervous system, this study will find the underlying mechanisms of Fear-focused Self-compassion Therapy for FCR, and provide implication for future research to develop more targeted intervention. Finally, this study will promote the implementation of Fear-focused Self-compassion Therapy for patients' FCR in Chinese background and investigate whether Chinese cancer patients could benefit from this therapy. However, in the present study without the third group with other intervention, it is not allowed to compare the effectiveness of Fear-focused Self-compassion Therapy with other intervention (i.e., mindfulness-focused therapy and cognitive behavior therapy).

Considering the lack of intervention research for young breast cancer patients, this study will contribute to the knowledge about how to decrease FCR in this population. Research into long-term effective psychological treatment for this population will be of great clinical value.

## Ethics statement

The studies involving human participants were reviewed and approved by Shaanxi Provincial Cancer Hospital Ethics Committee. The patients/participants provided their written informed consent to participate in this study.

## Abbreviations

FCR: Fear of cancer recurrence
RCT: Randomized controlled trial
FCRI: Fear of cancer recurrence inventory
SAS: Statistical analysis system
SCS: Self-compassion Scale
SCS: Self-compassion Scale
HRV: Heart rate variability
ECG: Electrocardiogram
CERQ-RS: Cognitive Emotion Regulation Questionnaire Rumination Subscale
CERQ-CS: Cognitive Emotion Regulation Questionnaire Catastrophizing Subscale
HADS: Hospital Anxiety and Depression Scale
QALY: Quality-adjusted life year
EQ-5D: EuroQol-5D
HRQoL: health-related quality of life
MCQ: Medical Consumption Questionnaire.
